## **4.2 STATISTICAL METHODS**

### **4.2.1 Methods for statistical analysis**

All patients enrolled in the study will be entered in the full analysis set independently of his/her treatment time. The intention to treat population will be considered for primary analysis. A descriptive statistical analysis will be performed to describe every relevant variable. In general, categorical data will be presented using counts and percentages, whilst continuous variables will be presented using the number of patients, mean, standard deviation, median, minimum, and maximum. Denominators for calculation of percentages will be taken as the number of non-missing responses in the specified analysis population and treatment group unless otherwise stated, and percentages will be rounded to one decimal. Minima and maxima will usually be reported to the same level of accuracy as the raw data; means, medians and standard deviations will be presented to one further decimal place; standard errors (if presented) will be presented to 2 decimal places more than the raw data. 97.5 % confidence interval will be calculated for primary outcome and for the relevant secondary ones. All data recorded in the CRF will be listed. Distribution of SAPSII and SOFA score (total and for single organ) at admission, P/F ratio distribution at baseline and at day 3, biomarkers PCR, PCT and IL-6 P/F ratio distribution at baseline and at day 3 will be summarized.

The comparison between

1. LMHW + steroids group and LMWH group
2. UHF + steroids group and LMWH group

with binary outcomes will be performed by using Relative Risks (RRs), whereas for continuous data, the difference of means (DMs) will be used. Comparisons involving time to event data will be displayed by using Kaplan-Maier survival curves and summarised by Hazard Ratios (HRs).

All measures of association will be presented with their confidence intervals. A result will be considered as statistically significant if its p-values will be less than 0.025 (2.5%).

The analyses will be performed by using STATA software.

As the study has not been sized to assess the difference between LMHW + steroids group and UHF + steroids group, the results obtained from this comparison will be reported and will be interpreted with caution. The main analyses will not take into account the factors of stratification.

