## **2.4 OUTCOMES**

### **2.4.1 Primary Endpoint:**

- All-cause mortality at day 28.

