### **2.6 SAMPLE SIZE**

The target sample size is based on the hypothesis that the combined use of UHF and steroids versus the LMWH group will significantly reduce the risk of 28-day death. The overall sample size in this study is expected to be 210 with a randomization 1:1:1. Assuming an alpha of 2.5% (two tailed) and mortality rate in LMWH group of 50%, as indicated from initial studies of ICU patients, the study will have an 80% power to detect at least a 25 % absolute reduction in the risk of death between:

a) LMHW + steroids group and LMWH group

or

b) UHF + steroids group and LMWH group

The study has not been sized to assess the difference between LMHW + steroids group and UHF + steroids group, therefore the results obtained from this comparison will need to be interpreted with caution and will need further adequately sized studies to be confirmed.

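### The main 28-day mortality comparison uses no baseline covariate although severity is collected, which gives up attainable power in a trial sized at exactly 80%

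*Protocol*

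**What the plan says.** The primary endpoint (protocol 2.4.1) is binary: "All-cause mortality at day 28". Section 4.2.1 sets out two comparisons, each steroid arm against LMWH alone, and says that the comparison "with binary outcomes will be performed by using Relative Risks (RRs), whereas for continuous data, the difference of means (DMs) will be used". No covariate is named. The section closes by stating that the main analyses will disregard the stratification factors, which section 3.1 gives as centre, BMI and age.

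Baseline severity appears in 4.2.1 only among the items to be summarised: "Distribution of SAPSII and SOFA score (total and for single organ) at admission, P/F ratio distribution at baseline and at day 3". Section 4.1 has SAPS II calculated from the first 24 hours of ICU stay. Appendix 4 has SOFA recorded daily from randomisation, and blood gases and inspired oxygen daily from inclusion.

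On size, section 2.6 says "The overall sample size in this study is expected to be 210 with a randomization 1:1:1" and that "the study will have an 80% power to detect at least a 25 % absolute reduction in the risk of death". It assumes a two-tailed alpha of 2.5% and a "mortality rate in LMWH group of 50%, as indicated from initial studies of ICU patients".

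**The concern.** Illness severity at entry is a plausible predictor of death by day 28. Where a baseline variable predicts the outcome, using it in the analysis reduces the variance of the treatment estimate without adding patients. The protocol plans to hold such variables and does not use them for the main estimate. It also expressly sets aside age, a stratification factor and a further candidate predictor.

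This matters more here than in a trial with a margin. The sample size has none: section 2.6 makes no allowance for loss of patients, although section 6.2 lets a patient ask for all of his or her data to be removed. At stake are a few points of power and a somewhat narrower 97.5% interval for the primary result.

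**Working it through.** **Inputs from the protocol.** Control mortality 50%; absolute reduction 25 points, so 25% in the active arm; two-sided alpha 0.025 per comparison, so z = 2.2414; power 80%, so z = 0.8416; 210 patients at 1:1:1, so 70 per arm (section 2.6). The pooled proportion is 0.375.

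**Step 1: reproduce the sample size.** Two proportions, pooled variance under the null, no continuity correction:

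n = [2.2414·√(2·0.375·0.625) + 0.8416·√(0.5·0.5 + 0.25·0.75)]² / 0.25²
= [2.2414·0.6847 + 0.8416·0.6614]² / 0.0625 = 69.97, rounded up to 70.

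3 × 70 = 210, the stated figure. Power at 70 per arm:

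Φ[(0.25 − 2.2414·√(0.46875/70)) / √(0.4375/70)] = Φ[(0.25 − 0.1834)/0.0791] = Φ(0.842) = 80.0%.

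With 5% or 10% of patients lost, the same formula gives 77.7% or 75.2%.

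**Step 2: power if baseline severity is used.** Let R² be the share of outcome variance that the baseline covariate explains. Adjustment multiplies the variance by about (1 − R²), so the effective size per arm is 70/(1 − R²). The protocol gives no value, so R² is an assumption shown over a range.

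| Assumed R² | Effective n per arm | Power |
|---|---|---|
| 0 | 70.0 | 80.0% |
| 0.05 | 73.7 | 82.2% |
| 0.10 | 77.8 | 84.5% |
| 0.15 | 82.4 | 86.6% |
| 0.20 | 87.5 | 88.8% |

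For orientation, a score with an AUC for death of about 0.65 to 0.75 corresponds to R² of about 0.06 to 0.19. The upper value holds at 50% mortality; at 25% mortality an AUC of 0.75 gives 0.16.

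**Step 3: check by simulation.** 6,000 trials per scenario, 70 per arm, 50% versus 25%. A Wald test on the crude log relative risk was compared with one on a relative risk standardised from a logistic model with treatment and one baseline score.

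| Assumed AUC | Crude RR | Standardised RR | Difference |
|---|---|---|---|
| 0.50 (useless) | 78.4% | 78.0% | −0.4 |
| 0.61 | 78.0% | 79.1% | +1.1 |
| 0.65 | 77.4% | 80.5% | +3.1 |
| 0.70 | 78.8% | 84.1% | +5.3 |
| 0.74 | 77.9% | 85.7% | +7.8 |

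Crude power lies slightly below 80% because this test works on the log relative risk, whereas the sample-size formula tests a difference in proportions. Simulation error is about 0.5 point (√(0.8·0.2/6000) ≈ 0.005). With equal mortality in both arms, each method rejected in 2.1% to 2.3% of trials, so the adjustment did not inflate the type I error.

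**The case against.** The strongest reply is that covariates are usually chosen in a statistical analysis plan, that the word unadjusted does not occur in section 4.2.1, and that a relative risk can be crude or standardised. Only the protocol was available for this review, so a separate plan may name a severity covariate. That part stands. But 4.2.1 does not leave the main analysis open: it fixes the effect measures, the 0.025 threshold, the 97.5% interval and the omission of the stratification factors, and it gives baseline severity a descriptive role only. The natural reading is a crude comparison, and a later plan that adjusted for age would depart from it.

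Four stronger readings are tempting and are not supported.

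- A reader might infer that chance imbalance in severity biases the crude relative risk. Under randomisation it does not. Such imbalance is sampling variability, which the interval and p-value already reflect.
- A reader might assume a correlation of 0.5 between severity and death (R² of 0.25) and claim a gain of about 11 points. The protocol gives no correlation, and that value needs an AUC of about 0.79 to 0.81. Eligibility also narrows severity (P/F of 150 or less, high D-dimer, more than 24 hours of ventilation), which may weaken prediction.
- A reader might extend the point to SOFA as an outcome. Section 2.4.2 defines new organ dysfunction and its grade, and no comparison of mean SOFA is stated.
- A reader might take all three measures as ready-made baseline covariates. They are not. SOFA is summarised at admission in 4.2.1 but recorded from randomisation in Appendix 4. The SAPS II window may not have closed at randomisation in every patient. P/F is cut off at 150.

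**Conclusion.** The point holds as a matter of efficiency. The crude analysis is valid, and nothing in section 2.6 is miscalculated. The trial has 80.0% power with no margin, and a prespecified adjustment could plausibly add about 2 to 9 points by the variance formula (R² from 0.05 to 0.20), or about 3 to 8 points in the simulation for an AUC of 0.65 to 0.74. With a weak score (AUC 0.61) the gain is about 1 point; with a useless one the loss is under half a point. All of these gains rest on an assumed prognostic strength that the protocol does not supply. The change is worth making before outcomes are seen, but the trial's validity does not depend on it.

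**What to change.** In section 4.2.1, make the main mortality estimate a marginal (standardised) relative risk and risk difference with 97.5% confidence intervals, from a logistic model with treatment and one baseline severity score. Define that score as the last total SOFA value before randomisation and before study treatment. Age may be added; if so, amend the sentence that leaves the stratification factors out of the main analyses. Standardising keeps the relative risk as the quantity estimated, which a logistic odds ratio would not. Keep the crude relative risk as a sensitivity analysis.

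Do not use SAPS II for only those patients whose 24-hour window has closed: a covariate defined for part of the sample is unworkable. P/F ratio need not be included, since the entry limit leaves it little room to add information.

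The cost is mainly wording. The covariate and a simple rule for missing baseline values must be fixed in advance. The eCRF instructions should state which SOFA value counts as baseline, because 4.2.1 and Appendix 4 describe different time points. No extra patients or visits are needed, and the model runs in Stata, the software already named.

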### **2.4.3 Physiological and Processes of care outcomes**

- Vital signs such as mean arterial pressure (MAP), heart rate (HR), respiratory rate (RR), diuresis and systemic body temperature and fluid balance will be recorded daily from inclusion until ICU discharge (censored day 28);
- Routine laboratory test parameters for organ function assessment: haemoglobin, platelets count, white blood cells count, troponin, coagulative parameters (INR, PT, aPTT), parameters for liver (AST, ALT, bilirubin) and renal function (creatinine) will be recorded daily from inclusion to ICU discharge (censored at day 28);
- Blood cells count, C-reactive protein (CRP), procalcitonin (PCT) and interleukin 6 (IL-6) will be recorded daily from inclusion to ICU discharge (censored at day 28);
- Ventilation mode, inspired oxygen fraction and arterial blood gas analysis parameters will be recorded daily from inclusion to ICU discharge from (censored at day 28);
- Adjunctive treatment such as pronation cycles, Nitric Oxide or ECMO will be recorded daily from inclusion to ICU discharge from (censored at day 28);
- New blood, respiratory and urinary-tract infections will be recorded from randomization to day 28;
- Viral reactivation measured by CMV DNA titres will be recorded from randomization to day 28;
- Need of new renal replacement therapy (intermittent haemodialysis or continuous veno-venous hemofiltration) from randomization to 28 days.

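### Section 4.2.1 gives one effect measure, the difference of means, for all continuous data and names no baseline covariate or log scale; read literally, this loses precision for P/F, CRP, procalcitonin and IL-6

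*Protocol*

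**What the plan says.** Section 4.2.1 defines two comparisons, each steroid arm against LMWH alone. It assigns relative risks to binary outcomes, hazard ratios to time-to-event data, and for the rest "whereas for continuous data, the difference of means (DMs) will be used". Significance is p below 0.025. The only statement on adjustment is "The main analyses will not take into account the factors of stratification"; those factors are centre, BMI and age (section 3.1).

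The one sentence in 4.2.1 that names the variables at issue is descriptive: "biomarkers PCR, PCT and IL-6 P/F ratio distribution at baseline and at day 3 will be summarized". In general, "continuous variables will be presented using the number of patients, mean, standard deviation, median, minimum, and maximum".

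Section 2.4.3 lists these variables as physiological and process-of-care outcomes: "C-reactive protein (CRP), procalcitonin (PCT) and interleukin 6 (IL-6) will be recorded daily from inclusion to ICU discharge", and "Ventilation mode, inspired oxygen fraction and arterial blood gas analysis parameters will be recorded daily from inclusion to ICU discharge". Appendix 4 gives a sparser schedule for the blood markers (daily to day 7, then days 14, 21 and 28), but it too starts at inclusion and covers day 3. Each follow-up value therefore has a baseline partner under either schedule.

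**The concern.** In a randomised comparison of a variable measured at entry and again later, part of the follow-up variance is predictable from the entry value. A plain difference of follow-up means leaves that part in the error term. If a marker is also strongly right-skewed, its arithmetic mean and standard error depend heavily on the largest values, and a proportional treatment effect is harder to see on the raw scale than on the log scale.

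The background in section 1.1 rests the case for steroids on a hyper-inflammatory response, and CRP, procalcitonin and IL-6 are the recorded measures of it. At about 70 per arm, an inefficient comparison could leave a real effect on them unclear. Naming the covariate and the scale in advance also prevents a choice between methods after results are seen, which is worth having in an open-label trial.

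**Working it through.** **1. The protocol's own figure.** Inputs from section 2.6: 50% mortality on LMWH, a 25-point absolute reduction, two-sided alpha 0.025, power 80%, allocation 1:1:1. With the pooled-variance formula:

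n per arm = [z(0.9875)·√(2·0.375·0.625) + z(0.80)·√(0.5·0.5 + 0.25·0.75)]² / 0.25²
= [2.2414·0.6847 + 0.8416·0.6614]² / 0.0625 ≈ 69.98, so 70 per arm and 210 in all.

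The stated 210 is reproduced. It concerns mortality only; the protocol gives no power figure for any continuous outcome, so nothing below changes it.

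**2. Baseline adjustment.** The baseline to follow-up correlation ρ is not in the protocol and is an assumption. Analysis of covariance multiplies the residual variance by 1 − ρ² and the interval width by √(1 − ρ²). Without adjustment, the difference detectable with 80% power at 70 per arm is (2.2414 + 0.8416)·√(2/70) = 0.521 SD.

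| ρ (assumed) | Variance removed | Interval narrower by | Detectable difference (SD) | Power for 0.5 SD |
|---|---|---|---|---|
| 0 (no adjustment) | 0% | 0% | 0.521 | 76.3% |
| 0.2 | 4% | 2% | 0.511 | 78.2% |
| 0.3 | 9% | 5% | 0.497 | 80.5% |
| 0.5 | 25% | 13% | 0.451 | 88.0% |

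Entry requires P/F of at most 150 and CRP (written PCR) of at least 6 times the upper limit (section 2.2.1). Such limits narrow the baseline range and may lower ρ, so those two variables may sit near the top of the table.

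**3. Scale, if the blood markers are right-skewed.** Assumptions: log-normal values, log-SD 0.8 to 1.3, a true 40% lower geometric mean (shift ln 0.6 = −0.511), 70 observed per arm, two-sided 0.025. On the log scale, power ≈ Φ(0.511 / (log-SD·√(2/70)) − 2.2414). For log-SD 1.0 this is Φ(3.02 − 2.24) = 78%. Raw-scale power and log-scale analysis of covariance come from simulation (6,000 trials per setting):

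| Log-SD (assumed) | Raw means | Log scale | Log scale + baseline, ρ = 0.3 | Log scale + baseline, ρ = 0.5 |
|---|---|---|---|---|
| 0.8 | 82% | 94% | 95% | 98% |
| 1.0 | 53% | 77% | 81% | 88% |
| 1.3 | 24% | 53% | 57% | 65% |

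Repeat simulations agree to within about 2 points. At log-SD 0.5 every method has power close to 100% for this effect, so the loss disappears when skew is mild. In this range more of the gain comes from the log scale than from the baseline covariate.

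**4. Attrition.** Step 3 takes all 70 per arm as observed. Recording of these variables stops at ICU discharge, and assumed control mortality is 50%, so later days have fewer values and less power under every method.

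**The case against.** The strongest reply is that the protocol makes no commitment to a poor test. A difference of means stands beside relative risks and hazard ratios, so it names an effect measure, and a baseline-adjusted model also yields a difference of means. The only adjustment ruled out is for the stratification factors. Covariates and transformations are commonly left to the statistical analysis plan, which is not at hand.

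Much of this stands, and it limits the point. A reader might infer more in four ways that the document does not support:

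- **That these four variables are to be compared by a raw, unadjusted difference.** Section 4.2.1 uses neither word, and its one sentence naming them plans a summary. The general rule would govern any comparison of them, because no other method is offered, but that is a literal reading.
- **That a few extreme values will dominate.** The protocol gives no SD or distribution for any marker. For P/F there is no basis in the document for assuming skew.
- **That the CRP entry criterion shows skew.** A multiple of the local upper limit puts different laboratories on a common footing; it says nothing about distribution.
- **That these outcomes test a stated objective.** The only objective (section 1.2) is 28-day mortality. The markers are outside the primary and secondary lists, and 97.5% intervals are promised only for the primary and relevant secondary outcomes.

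The reply does not remove the point. The rule is stated for all continuous data, it gives no lead towards the available baselines, and a ratio of geometric means would depart from the stated measure. A later plan could therefore add a covariate without conflict, but could not move to log-scale ratios without departing from the protocol.

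**Conclusion.** The point holds as one of efficiency. Read literally, the rule for continuous data is less precise than a method that uses values already collected. Randomisation protects it from bias. The primary endpoint and the total of 210 are unaffected, and ventilation-free and ICU-free days have no baseline value, so adjustment of this kind does not arise for them.

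The loss from ignoring baseline is small to moderate: 4% to 25% of the variance for ρ from 0.2 to 0.5, with P/F and CRP possibly at the low end. The loss from the raw scale could be large for CRP, procalcitonin and IL-6 (82% to 24% power against 94% to 53%), but only if they are as skewed as assumed. Correlation, log-SD and effect size are all assumptions. Severity is low.

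**What to change.** Add to section 4.2.1, after the sentence on differences of means:

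*Where continuous outcomes with a baseline measurement are compared between arms (for example at day 3, the time point already summarised), the comparison is by analysis of covariance with the baseline value as covariate; CRP, PCT and IL-6 are log-transformed and reported as ratios of geometric means.*

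The baseline of the three markers should be log-transformed as well, as in the calculation above. Day 3 suits the purpose because section 4.2.1 already summarises "P/F ratio distribution at baseline and at day 3", and fewer patients will have died or left ICU by then than at later days. The sentence does not settle how later days should treat those patients.

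Cost: one sentence and no new data, with the ethics committee notification and written authorisation that section 6.1 requires for any protocol change. The drawback is that three markers are reported as ratios rather than differences.

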- Routine laboratory test parameters for organ function assessment: haemoglobin, platelets count, white blood cells count, troponin, coagulative parameters (INR, PT, aPTT), parameters for liver (AST, ALT, bilirubin) and renal function (creatinine) will be recorded daily from inclusion to day 7 and then at day 14, 21, 28, censored at ICU discharge;
- Blood cells count, C-reactive protein (CRP) and procalcitonin (PCT), IL-6, immunoglobulins titers (IgG, IgA, IgM) will be recorded daily from inclusion to day 7 and then at day 14, 21 and 28, censored at ICU discharge;
- Beta-D Glucan in the blood and/or Galactomannan in the BAL will be recorded at admission and then every 3-5 days, censored at ICU discharge
- Ventilation mode (spontaneous breathing or mechanical ventilation), inspired oxygen fraction and arterial blood gas analysis parameters will be recorded daily from inclusion to ICU discharge, censored at day 28;
  - Adjunctive treatment such as pronation cycles, Nitric Oxide or ECMO will be recorded daily from inclusion to ICU discharge from (censored at day 28);
- New blood, respiratory and urinary-tract infections and the implicated microorganisms will be recorded from randomization to day 28;
- Viral reactivation measured by ADENOVIRUS, HSV e CMV DNA titres will be recorded from randomization to day 28, censored at ICU discharge;
- Need of renal replacement therapy: from randomization to 28 days, censored at ICU discharge.

D) Primary Outcome:

- All-cause mortality will be measured at day 28.

E) Secondary Outcomes:

- All-cause mortality will be measured at ICU discharge and hospital discharge
- SOFA score and its components will be recorded daily from randomization to ICU discharge (censored at day 28);
- Ventilation free days (VFDs) at day 28, measured at day 28;
- ICU free days (IFDs) at day 28, measured at day 28;
- Need of rescue administration of high-dose steroids or immune-modulatory drugs, measured from randomization to ICU discharge, censored at day 28;
- Switch from non-invasive to invasive mechanical ventilation from randomization to ICU discharge, censored at day 28;
- Occurrence of new infections will be recorded from randomization to day 28;
- Occurrence of objectively confirmed venous thromboembolism, stroke or myocardial infarction will be recorded from randomization to day 28;
- Occurrence of protocol related adverse events (see chapter 5.2) at day 28 (safety endpoint).

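### Section 4.2.1 assigns all time-to-event comparisons to Kaplan-Meier; for the non-fatal delay to invasive ventilation this overstates incidence, and unequally between arms, because death precludes the switch

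*Protocol*

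**What the plan says.** Section 4.2.1 of the protocol names three routes for comparing each steroid arm with the LMWH arm: relative risks for binary outcomes, differences of means for continuous data, and, for timed data, "Comparisons involving time to event data will be displayed by using Kaplan-Maier survival curves and summarised by Hazard Ratios (HRs"). The third route has no exception, and the section does not say how death is handled when the event is non-fatal.

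The secondary endpoints are in section 2.4.2. Most non-fatal ones are worded as an occurrence or a need: rescue drugs, switch to invasive ventilation, new infection, new organ dysfunction, thromboembolism, stroke or infarction, bleeding. One is worded as a time: the delay from starting non-invasive ventilation to the switch to invasive ventilation.

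Appendix 4 sets recording windows, for example "Need of rescue administration of high-dose steroids or immune-modulatory drugs, measured from randomization to ICU discharge, censored at day 28" and, for viral reactivation, "DNA titres will be recorded from randomization to day 28, censored at ICU discharge". Death is not mentioned in these windows.

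Section 2.6 supplies the death rates. It assumes a "mortality rate in LMWH group of 50%, as indicated from initial studies of ICU patients", and states that "the study will have an 80% power to detect at least a 25 % absolute reduction in the risk of death". The design therefore compares 50% with 25%.

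**The concern.** Kaplan-Meier treats a censored patient as someone who could still have the event later. That cannot be so for a patient who died before the switch. Read as an incidence, 1 minus Kaplan-Meier then estimates how many would have switched had nobody died, which is more than the proportion who do switch.

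The excess grows with mortality. If the treatment works as the design supposes, the control arm loses twice as many patients to death, so its curve is inflated more than a steroid arm's. The displayed gap between arms then mixes the effect on the switch with the effect on death. At stake is the reading of a secondary endpoint on respiratory course, in a trial where death is expected to be common and to differ by arm.

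**Working it through.** **Inputs from section 2.6.** "The overall sample size in this study is expected to be 210 with a randomization 1:1:1", so 210 / 3 = 70 per arm; "Assuming an alpha of 2.5% (two tailed) and mortality rate in LMWH group of 50"%; 80% power; a 25-point absolute reduction, so 50% − 25% = 25% in a steroid arm. Mortality is measured over 28 days (section 2.4.1).

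**Inputs assumed.** The protocol gives no rate for the switch or any other non-fatal event. A switch hazard λ of 0.5%, 1% or 2% per day is assumed, equal in the two arms. Hazards are taken as constant and independent over 28 days, with the death hazard before a switch equal to the overall one.

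**Step 1: reproduce the plan's own figure.** With pooled variance and no continuity correction,

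n = [z(0.9875) √(2 × 0.375 × 0.625) + z(0.80) √(0.5 × 0.5 + 0.25 × 0.75)]² / 0.25²
= [2.2414 × 0.6847 + 0.8416 × 0.6614]² / 0.0625 = 69.97.

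This rounds up to 70 per arm and 210 in total, with 80.0% power. So 50% against 25% is indeed the design assumption.

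**Step 2: death hazards.** μ = −ln(1 − mortality) / 28. Control: 0.6931 / 28 = 0.02476 per day. Steroid arm: 0.2877 / 28 = 0.01027 per day.

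**Step 3: the two estimates at day 28.**
- 1 minus Kaplan-Meier, deaths censored: 1 − exp(−28λ)
- Cumulative incidence, death competing: λ / (λ + μ) × [1 − exp(−28(λ + μ))]

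Worked case, control, λ = 0.01: 1 − exp(−0.28) = 24.4%; 0.01 / 0.03476 × [1 − exp(−0.9731)] = 0.2877 × 0.6221 = 17.9%. The difference is 6.5 points.

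| λ per day | 1 − KM, both arms | Incidence, control | Excess, control | Incidence, steroid | Excess, steroid |
|---|---|---|---|---|---|
| 0.5% | 13.1% | 9.5% | 3.6 | 11.4% | 1.7 |
| 1% | 24.4% | 17.9% | 6.5 | 21.4% | 3.1 |
| 2% | 42.9% | 31.9% | 11.0 | 37.8% | 5.1 |

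Excess is in percentage points, taken before rounding.

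**Step 4: dependence on the assumed rate.** With 1 minus Kaplan-Meier varied from 5% to 50%, it exceeds the incidence by a factor of 1.38 falling to 1.33 in control, and 1.15 falling to 1.13 in a steroid arm. The relative excess hardly depends on λ.

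**Step 5: effect on the contrast.** With equal hazards the two Kaplan-Meier curves coincide, so no false gap appears, although both levels are too high. If instead the true incidence is 20% in both arms, 1 minus Kaplan-Meier shows 27.2% against 22.9%: a gap of 4.3 points in favour of the steroid arm where the proportions switching are the same. The cause-specific hazard ratio in that case is 0.82.

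**The case against.** The strongest objection is about scope. A reader might infer that infection, bleeding, thromboembolism, rescue treatment and the occurrence of a switch all go to Kaplan-Meier. The protocol does not say so. They are worded as occurrences or needs, and section 4.2.1 sends binary outcomes to relative risks. A relative risk on all randomised patients compares crude incidences and has no Kaplan-Meier overstatement. This part of the objection stands in full.

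The term for censoring in Appendix 4 does not widen the scope either. The same term is applied to vital signs, laboratory tests and ventilation mode, so it marks the end of a recording window and not an analysis rule.

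Two further readings are tempting and also fail:
- That the relative risk is itself biased against the steroid arms. With equal daily hazards it would be 1.18 to 1.20, but that is simply the ratio of the true incidences. It needs interpretation alongside mortality; it is not an error.
- That the hazard ratio is wrong. With deaths censored it is a valid cause-specific hazard ratio. It needs that label and should not be read as a ratio of incidences.

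It can also be said that the handling of death belongs in a statistical analysis plan, which is not at hand, and that the delay might be analysed as a continuous variable among those who switched. The first carries some weight, but the protocol does not leave the method open: it fixes one for all timed comparisons. The second is possible, but the protocol does not state it.

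**Conclusion.** The point holds in a limited form. Kaplan-Meier is right for all-cause mortality. As a display of incidence it is a poor choice for a non-fatal endpoint analysed over time, which means at least the delay to invasive ventilation. The primary endpoint and the sample size are unaffected.

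At the protocol's own mortality assumptions the overstatement is 3.6 to 11.0 points in control and 1.7 to 5.1 points in a steroid arm, or about 33–38% and 13–15% in relative terms over the wider sweep of rates. These sizes illustrate the problem and do not predict the result. They rest on an assumed switch hazard, on constant and independent hazards, and on design mortality that applies to all randomised patients. The delay concerns only patients on non-invasive ventilation, whose number and mortality the protocol does not give. If most deaths in that subgroup follow a switch instead of preceding it, the excess is smaller. With all 70 patients per arm at risk, the control excess would be about 1.0 to 2.0 standard errors of the incidence; with fewer at risk, the same excess is fewer standard errors.

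**What to change.** Amend section 4.2.1 so that:
- Kaplan-Meier curves are used for all-cause mortality.
- The delay to invasive ventilation, and any other non-fatal endpoint shown over time, is displayed as cumulative incidence (Aalen-Johansen) with death as a competing event, and with ICU discharge alive as a further competing event where recording ends there.
- The hazard ratio for such an endpoint is labelled cause-specific and given with its 97.5% confidence interval.
- The proportion who die without the event is shown by arm beside it.

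The cost is one or two sentences, a little more analysis, and one extra summary for each endpoint concerned. The design, sample size and list of endpoints stay as they are.
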